### Strategies to improve adherence to interventions {11c}

To minimize data loss, all participants will be guided when they sign the informed consent form and commit to attending on the scheduled treatment dates. Participants will receive an appointment card for scheduled sessions. An evaluator will be responsible for notifying and monitoring the participants weekly (via telephone contact, text message, and/or email) and accompanying them during the research. In cases of abandonment or impossibility of continuing the study, the data will be analyzed according to an intention-to-treat protocol.

### Relevant concomitant care permitted or prohibited during the trial {11d}

During the experiment, concurrent treatments for chronic diseases such as diabetes and hypertension will be accepted. Throughout the trial, participants will be asked not to start any other interventions or pain medications as it may influence outcomes.

### Provisions for post-trial care {30}

The interventions are designed to inflict minimal to no harm, and no compensation for harm is deemed necessary.

### Outcomes {12}

The primary outcome will be pain intensity at rest and with movement, determined using the NPRS. The secondary outcomes will be pressure pain threshold (PPT), heat pain threshold (HPT), temporal summation (TS) of pain, conditioned pain modulation (CPM), sit-to-stand test, and repeated trunk flexion. CPM will be used to assess descending inhibition. Sit-to-stand and repeated trunk flexion will be used to assess function. These outcomes will be measured twice, once as a baseline testing, and then again post-treatment.

#### Numeric pain rating scale (NPRS)

Resting pain intensity and pain with movement (during the sit-to-stand and repeated flexion tests) at the lumbar spine will be assessed before and after intervention (primary outcome measures). We will be using an 11 point NPRS for pain intensity measurements. Pain scores range from 0 representing “no pain” and 10 representing the “worst pain imaginable” [20].

#### Sit-to-stand test

The sit-to-stand test is a test of strength for the lower body. Five sit-to-stand repetitions will be completed in two trials, with an average of two trials for scoring [21]. The time it takes to complete five repetitions as quickly as possible will be recorded. This test has good reliability (ICC > 0.95) and validity (*r* = 0.59 to 0.88) [21]. The test will be conducted before and after the treatment session to assess a change in speed of sitting to standing, representing a functional change concerning lower extremity strength in response to TENS. The participants will be asked to rate pain at the end of test.

#### Repeated trunk flexion

From a neutral standing position, the subject will be required to flex the trunk to the limit of the trunk flexion range of motion and return to the upright position as fast as tolerable. This activity will be repeated ten times, and the total procedure will be timed with a stopwatch [22, 23]. The task will be repeated after a 30-s pause, and the average time of the two tasks will be the resulting score [21, 23]. This test has good reliability (ICC 0.89) [22]. The participants will rate pain at the end of test.

#### Pressure pain threshold (PPT)

A digital pressure algometer will measure the pain threshold to deep mechanical stimuli. The AlgoMed Computerized Pressure Algometer from the manufacturer Medoc will be utilized. This digital pressure pain algometer is a hand-held, software-based device that provides real-time visual and auditory feedback. The software provides a graphic display of the test displaying the applied pressure rate, to help ensure a constant rate is being applied. The device also provides an auditory cue for when the button has been activated. A 1-cm^2^ algometer probe will apply pressure at 40 kPa/s. Participants will be instructed to activate a button when the sensation of pressure becomes painful, and this value will be recorded. This method will register mean pressure pain thresholds in the lumbar region, forearm, and leg. The intra-rater reliability of the measurement of PPT will be performed in 10 asymptomatic subjects by a single evaluator at 48-h intervals. Reliability will be estimated by calculating the intraclass correlation coefficients (ICCs).

Measures will be done over 2 points marked bilaterally with a permanent marker, the first located 5 cm lateral to the L3 spinous process [24] and the second 5 cm lateral to the L5 spinous process [25]. In addition, a point will also be marked over the anterior tibialis muscle of the right and left leg 5 cm from the tibial tuberosity [26, 27]. There will also be a point marked and measured on the right and left extensor carpi radialis muscle, 5 cm distal from the elbow crease.

#### Heat pain threshold (HPT)

Superficial heat pain sensitivity will be assessed using a handheld thermode (Medoc TSA-II, Israel) with a single 30 × 30-mm probe placed in the midline for each lumbar segment (L5 and L3) centered at the spinous process ensuring complete contact between skin surface and probe. The baseline temperature will be pre-set to 32°C. During testing, the temperature will increase at a rate of 1 °C/s until the participant reports the temperature as painful by pressing an indicator button. Maximum temperature will be pre-set at 50 °C; if no pain had been elicited by then, this will be recorded as the heat pain threshold [28]. Using the thermode to indicate the HPT has excellent intra-rater reliability (ICC 0.86 to 0.93) when tested at the spine of asymptomatic volunteers [29].

The PPT and HPT recordings will be performed, with the patient in the seated position, at each spinal segment three times. The segments will be tested in a pre-determined, computer-generated, random order with 10-s rest intervals between each test. In addition, before data collection, two test trials of each pain threshold assessment will be performed at the dominant forearm to familiarize participants with the procedure [28].

#### Temporal summation (TS)

TS will be induced by a pressure algometer. The intra-rater reliability of pain TS will be tested in 10 asymptomatic participants by a single evaluator at 48-h intervals. Reliability will be estimated by calculating the ICCs. The area selected for TS analysis will be the site indicated as the lower pain threshold in the low back algometry. Ten stimuli will be performed using the algometer on the selected region. Each TS stimulus will be maintained for 1 s before being released, and the stimuli will be spaced at 1-s intervals. Participants will be instructed to report pain using the NRS at the first, fifth, and tenth stimulus [30]. The TS assessment will be performed before and after TENS application.

#### Conditioned pain modulation

A cold pressor test will be used to assess the activation of the conditioned pain modulation [31]. An ARTIC A25 Refrigerated Circulator (Thermo Scientific, Newington, NH, USA) will be the instrument used to administer the cold pressor test. The cold pressor test is as follows: The subject will have PPT on one point of their low back before immersion. Then, CPM will be induced by immersing the participants’ dominant hand up to the wrist into a 5 °C refrigerated circulating water bath. After 20 s, they will then be asked to rate the pain of their dominant hand as it is still immersed on a 0 to 10 scale. The PPT at the low-back algometry point will be recorded 30 s after immersion while the participants hand remains immersed. The magnitude of CPM will be assessed by calculating the PPT variation from pre-immersion values, where positive values represent hypoalgesia and negative values represent hyperalgesia.

#### Study blinding assessment

To assess the blinding of the outcomes assessor, the assessor will be asked, “What treatment did the subject receive today?” The choices for the outcome assessor will be: active TENS, placebo TENS or no TENS. The responses to these questions will be recorded and compared to assess the blinding of the outcomes assessor.

### Participant timeline {13}

Participants will be asked to complete a self-administered questionnaire that collects demographic information such as age, sex, marital status, education level, ethnicity, race, income, and history of surgeries. Weight will be measured using a calibrated electronic scale, height will be measured using a stadiometer, and the body mass index will be calculated. Participants will be randomized to treatment group order after providing written consent. The order of active TENS, placebo TENS and no TENS will be randomized via the website (randomization.com). Simple randomization results will be concealed in sealed opaque envelopes with consecutive numbers and will not be available to the outcomes assessor. The envelopes will be signed, dated, and opened by the TENS allocator before the TENS application and after the outcomes assessor has left the room.

An overview of the study procedures is shown in Fig. 1.

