**Methods/design:**

This study will be a randomized crossover trial. The participants for this study will be recruited from various places, including the University of Hartford, physical therapy clinics, and local businesses in the Hartford area, as well as online websites geared towards clinical trial recruitment. A total of 34 participants will receive all three treatments: active TENS, placebo TENS, and no treatment control. The treatment order will be randomized using a website-based randomization tool. For active TENS, a modulating frequency of 2–125 Hz will be applied with a variable pulse duration and maximal tolerable intensity for 30 min. The TENS will be left on for post-treatment testing to assess the effects during its maximally effective period for a total of 50 to 60 min. Furthermore, the intensity may be turned down if muscle twitching is present to ensure blinding of the evaluator. For placebo TENS, the unit will deliver current for 45 s, ramping to 0 in the last 15 s. The primary outcome will be pain intensity at rest and with movement, determined using the numerical pain rating scale. The secondary outcomes will be pressure pain threshold, heat pain threshold, temporal summation of pain, conditioned pain modulation, sit-to-stand test, and repeated trunk flexion. The assessments will be performed immediately before and after treatment. Statistical analysis of the data obtained will consider a significance level of *p* < 0.05.

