### Sample size {14}

Sample size was calculated to determine the total number of study participants needed to detect a difference of 2 points for the pain intensity outcome, which is considered a clinically relevant value for LBP [32], as measured using the NPRS, with a standard deviation of 1.9 points [13]. An 80% statistical power, 5% alpha, and a possible sample loss of 15% were considered. Thus, a total of 34 participants will be needed. This calculation was performed using Minitab v.17 software (State College, PA, USA).

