## Assignment of interventions: allocation

### Sequence generation {16a}

The order of active TENS, placebo TENS and no TENS will be randomized via the website (randomization.com).

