## Statistical methods

### Statistical methods for primary and secondary outcomes {20a}

An assessor blinded to the randomization and assessment processes will perform the data analysis for the primary and secondary outcomes. The intention-to-treat principle will be adopted in the analyses. Descriptive statistics (mean, standard deviation, 95% confidence intervals) will be generated for all variables. Normality will be evaluated using the Kolmogorov–Smirnov test and the Levene’s test will be used to assess for homogeneity of variance. Repeated measures ANOVA and the Tukey test will be used for normally distributed data. The Friedman test, followed by post hoc pairwise comparisons using the Wilcoxon Signed Ranks test, will be used if data are not normally distributed. Cohen’s d test will be used to calculate the effect size for normally distributed data and it was classified as small (0.0–0.2), moderate (0.3–0.5), or large (≥ 0.6) [33]. For non-normally distributed data the effect size will be calculated by the Cliff’s delta classified as small (0.147 ≤ 0.330), medium (0.330 ≤ 0.474), or large (≥ 0.474) [34]. These analyses will be performed using the SPSS v.28 statistical software (SPSS, Inc., IL, USA). Statistical significance will be considered at *p* <  0.05.

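### Simple randomisation of 34 people to six treatment orders is likely to leave the orders uneven, which costs some precision if sessions differ; permuted blocks with period in the model would recover it

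*Protocol article*

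**What the plan says.** The abstract of the protocol article fixes the size and the design: "A total of 34 participants will receive all three treatments: active TENS, placebo TENS, and no treatment control". The Participant timeline section gives the allocation method: "Simple randomization results will be concealed in sealed opaque envelopes with consecutive numbers". The Sequence generation section repeats the website, "The order of active TENS, placebo TENS and no TENS will be randomized via the website", without the word simple and without any blocking, Latin square or other balancing of orders. The number of orders is not stated; six follows from three conditions.

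The statistical methods section names the analysis: "Repeated measures ANOVA and the Tukey test will be used for normally distributed data", with Friedman and Wilcoxon tests if normality fails. It mentions no period term, and the section on additional analyses plans no adjusted analysis. Every outcome is measured before and after treatment in each session.

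**The concern.** A crossover compares conditions within a person, but each condition is also tied to a session. Every visit repeats pain ratings, two movement tests, pressure and heat thresholds, temporal summation and a cold pressor test, so practice, habituation or familiarity with the setting could make the first visit differ from later ones. If active TENS falls in the first session more often than placebo, part of that difference enters the treatment contrast. Using all orders about equally often prevents this by design. Independent draws for 34 people over six orders do not.

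The allocation list is made before the first session, so a later analysis plan cannot change how uneven it is; it can only adjust for it. What is at stake is the precision of active minus placebo, and how evenly people are split between meeting active before and after placebo.

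**Working it through.** **Inputs.** From the article: 34 participants, three conditions, simple randomisation, target difference 2 points, and, from the sample size section, "with a standard deviation of 1.9 points". Assumed: six equally likely orders drawn independently; 1.9 read as the SD of the paired difference (the article does not say which SD it is); session effects of illustrative size, since the article gives none.

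**The plan's own figure.** The article gives no figure for balance. Its total of 34 is close to a two-group formula: 2 × (1.96 + 0.84)² × 1.9² / 2² = 14.1, so 15 per arm and 30 in all; 30 × 1.15 = 34.5. That derivation is a separate matter. Here 34 is only an input.

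**Order counts.** The expected count is 34/6 = 5.67. In 200,000 simulated multinomial allocations:
- some order has 2 or fewer people in 34%;
- some order has 10 or more in 27%;
- the gap between largest and smallest order averages 6.0;
- the most even split possible (6, 6, 6, 6, 5, 5) occurs in 0.4%;
- active TENS is in session 1 for 6 to 17 people (95% range, expected 11.3);
- active comes before placebo for 11 to 23 people, that is 32% to 68%.

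With blocks of six, five full blocks plus four people give active first in 10 + (0 to 2) = 10 to 12, and active before placebo in 15 + (1 to 3) = 16 to 18, or 47% to 53%.

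**Effect on the contrast, first-session effect d.** For one person, active minus placebo is shifted by +d, 0 or −d with probability 1/3 each, so the variance is 2d²/3. Over 34 people the mean shift has expectation zero and SD d × √(2/(3 × 34)) = 0.140d.

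**Effect on the contrast, steady drift s per session.** The active-minus-placebo gap in session number is ±1 (probability 4/6) or ±2 (probability 2/6), so its variance is (4 × 1 + 2 × 4)/6 = 2. The SD of the mean shift is s × √(2/34) = 0.243s.

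**Standard error of active minus placebo.** With no session effect it is 1.9/√34 = 0.326. Under simple randomisation without a period term:

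| Assumed session effect | SD of shift | Standard error |
|---|---|---|
| First session, 0.25 point | 0.035 | √((3.61 + 0.042)/34) = 0.328 |
| First session, 0.5 point | 0.070 | √((3.61 + 0.167)/34) = 0.333 |
| First session, 1 point | 0.140 | √((3.61 + 0.667)/34) = 0.355 |
| Drift, 0.5 point per session | 0.121 | √((3.61 + 0.5)/34) = 0.348 |
| Drift, 1 point per session | 0.243 | √((3.61 + 2)/34) = 0.406 |

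For the 1-point first-session effect the 95% range of the shift is about ±0.26 points. Blocks of six limit it to 2/34 = 0.06.

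**Does the test stay valid?** Each person's difference already contains its own random session effect, so the usual standard error includes it. In simulated paired t-tests without a period term, type I error under simple randomisation was about 5% for a 1-point first-session effect and for a 1-point drift. With blocks but no period term, the true standard error falls but the estimated one does not (about 0.353 for the 1-point first-session effect), and type I error drops to about 3.3%. The test becomes conservative, so blocking gives its full gain only with period fitted.

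**Cost of fitting period.** Over simple allocations, the variance of active minus placebo rises by about 3% on average (95th percentile 10%), giving a standard error of 0.326 × √1.03 = 0.331 whatever the session effect. With equal orders, period and treatment are orthogonal and this cost disappears.

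**The case against.** Simple randomisation is a valid method, and the strongest case is that nothing here needs repair. The shift averages zero, is already in the standard error, and is small beside 2 points: 0.14 is 7% of the target even under an assumed 1-point first-session effect. Each session has its own pre-treatment assessment, so if change scores are analysed, a session effect on the level of pain cancels. Model terms are commonly left to an analysis plan that is not shown here. Recruitment was planned for August 2023 to August 2024 and the article appeared in April 2024, so many participants may already have been allocated. All of this stands. It limits the point to precision and to an inexpensive improvement.

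Four stronger readings are tempting and are not supported.
- A reader might infer that the treatment effect is biased by session. The error has mean zero over allocations and the test holds its level.
- A reader might infer that uneven orders cause the problem of prior exposure to active TENS. With perfectly balanced orders half the participants still meet active before placebo. For an assumed carry-over of 1 point, the bias is 0.50 when balanced and 0.33 to 0.67 (95% range) under simple randomisation, so the main part is untouched by blocking.
- A reader might infer that order checks become uninformative. They become less precise, but the roughly 3% variance cost shows that period remains well separable from treatment.
- A reader might treat the unnamed period term as an error in itself. A condensed article need not list it.

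What does not fall away is that the article states the allocation method outright, and an analysis plan cannot make the list more even. The wording may also be loose: if the list in use was in fact balanced, the article should say so.

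**Conclusion.** The point holds as a matter of efficiency. Simple randomisation of 34 people to six orders is likely to leave them uneven, with an order of 2 or fewer people in about a third of allocations. If 15% are lost, leaving 34 × 0.85 ≈ 29 completers, that rises to 58%. The price is a larger standard error for active minus placebo: 0.355 instead of about 0.33 for a 1-point first-session effect, 0.406 instead of about 0.33 for a 1-point drift per session, and almost nothing for an effect of 0.25 point. The loss is smaller again if within-session change is analysed. Significance tests are not invalidated.

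Balanced orders would narrow the share meeting active before placebo from 32%–68% to 47%–53%. They would not remove carry-over or recognition of placebo. The counts are firm given independent, equally likely draws. The sizes in points rest on assumed session effects, and the standard errors also on reading 1.9 as the SD of the paired difference.

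**What to change.** In the Participant timeline and Sequence generation sections, replace simple randomisation, for every participant not yet allocated, with permuted blocks that each contain all six orders (size 6 or 12, not disclosed to recruiting and assessing staff). Keep the sealed, numbered envelopes. Include period as a fixed effect in the primary model, because blocking without it makes the test conservative. The Friedman and Wilcoxon route has no period term in its standard form, so it would not gain in the same way.

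The cost is one new list from the independent researcher. The last orders in a block become slightly more predictable, which matters little when everyone receives all three conditions. If no session effect exists, fitting period costs about 3% in variance on average with a simple list, and close to nothing with balanced orders. If most participants are already allocated, blocking the remainder cannot restore balance, and the period term carries most of the benefit.

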**Fig. 1 Fig1:**
[figure not shown]
Schedule of enrolment, interventions, and assessments

### Sample size {14}

Sample size was calculated to determine the total number of study participants needed to detect a difference of 2 points for the pain intensity outcome, which is considered a clinically relevant value for LBP [32], as measured using the NPRS, with a standard deviation of 1.9 points [13]. An 80% statistical power, 5% alpha, and a possible sample loss of 15% were considered. Thus, a total of 34 participants will be needed. This calculation was performed using Minitab v.17 software (State College, PA, USA).

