### Trial design {8}

The study will be a crossover design and will be conducted at the University of Hartford. The study protocol was approved by the Institutional Review Board (IRB) of the University of Hartford, it was registered online on ClinicalTrials.gov, and will be reported according to CONSORT guidelines [16]. The protocol was developed following the recommendations of SPIRIT (Standard Protocol Items: Recommendations for Interventional Trials). The RCT will have a blinded evaluator.

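### The stated 34 participants for 80% power does not follow from the stated inputs in this three-condition crossover; a paired calculation needs 12 to 20 including loss

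*Protocol article*

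**What the plan says.** The design is stated twice. The Trial design section says "The study will be a crossover design and will be conducted at the University of Hartford", and the Abstract says "A total of 34 participants will receive all three treatments: active TENS, placebo TENS, and no treatment control". The Statistical methods section plans a within-person analysis: "Repeated measures ANOVA and the Tukey test will be used for normally distributed data".

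The Sample size section describes the number as that "needed to detect a difference of 2 points for the pain intensity outcome", with an SD of 1.9 points taken from a cited study, and adds: "An 80% statistical power, 5% alpha, and a possible sample loss of 15% were considered". It ends: "Thus, a total of 34 participants will be needed".

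The section does not say whether 1.9 is the SD of a single score, of a pre-post change or of a within-person difference. It names no contrast, gives no within-person correlation, and does not say whether the 5% is one- or two-sided.

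**The concern.** In a crossover each comparison of conditions is made within a person. Its precision depends on the SD of the paired difference and on the number of people, not on the number per group. The paragraph gives a full set of inputs and a result, but nothing in it reflects pairing, and the result looks too large for a paired comparison with those inputs.

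Two things are at stake. A reader told that the trial has 80% power for 2 points will misjudge its sensitivity: it could detect differences well below the value the protocol calls clinically relevant. The stated 80% also hides how much room there is for adjustment over the pairwise comparisons.

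**Working it through.** **Inputs.** From the Sample size section: difference 2, SD 1.9, power 80%, alpha 5%, loss 15%, total 34. Assumed: two-sided alpha, and a between-session correlation r of 0 to 0.5, because the protocol gives neither. Completers: 34 × 0.85 = 28.9, taken as 29.

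**1. Can 34 be reproduced?** Two parallel groups, normal approximation:

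n per group = 2 × (1.960 + 0.842)² × 1.9² / 2² = 14.17, so 28.3 in total, and 28.3 / 0.85 = 33.3, rounded up to 34.

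Other routes to a total:

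- Same formula, rounded per group first: 15 × 2 = 30, then 30 / 0.85 = 35.3, so 36 (or 35 by multiplying by 1.15).
- Exact two-sample t: 16 per group (82.1% power; 15 gives 79.5%), 32 in total, 38 with loss.
- One-sided parallel groups: 28 or 29 with loss.
- One-way ANOVA with three groups and a maximum difference of 2: 19 per group, 57 in total, 68 with loss.

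**2. What does the crossover need?** Paired t-test, noncentral t, with SD of the difference = 1.9 × √(2(1 − r)).

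- If 1.9 is itself the SD of the difference (equivalent to r = 0.5): 9 completers give 78.9% and 10 give 84.1%. So 10, and 10 / 0.85 = 11.8, or 12 with loss.
- If 1.9 is a single-session SD and r = 0, the SD of the difference is 1.9 × √2 = 2.687: 16 completers give 79.5% and 17 give 82.1%. So 17, and 17 / 0.85 = 20 with loss.

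Neither gives 34.

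**3. What does 34 deliver with 29 completers?** One unadjusted two-sided 5% paired test for a 2-point difference:

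| r | SD of difference | Power | Difference detectable at 80% power |
|---|---|---|---|
| 0 | 2.687 | 97.2% | 1.45 |
| 0.3 | 2.248 | 99.6% | 1.21 |
| 0.5 | 1.900 | 99.98% | 1.02 |

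For r = 0 the noncentrality is 2 / (2.687 / √29) = 4.01, against a critical t of 2.048 on 28 degrees of freedom.

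**4. With adjustment over the three pairs, r = 0, 29 completers.** The Tukey critical value of 2.408 gives 94.2%. Bonferroni at 0.05 / 3 gives 92.0%.

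**5. What would make 80% true?** With 28 to 29 completers, 80% power for 2 points needs an SD of the difference of about 3.6 to 3.7, nearly twice the only SD given. One route reaches that size. Suppose 1.9 is a single-score SD, the endpoint is the pre-post change, and all four scores in a contrast are uncorrelated. The SD of the difference is then 1.9 × √4 = 3.8, and power is 78.1% at 29 completers (76.6% at 28). With a pre-post correlation of 0.5, each change has SD 1.9 × √(2 × 0.5) = 1.9. The contrast of two uncorrelated changes is then back at 2.687, and power is 97.2%.

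**The case against.** The strongest reply is that the 97% to 99.9% range is conditional. It assumes that 1.9 is a single-session or paired-difference SD, and that there is one unadjusted contrast. The source of the 1.9 is not available here, and the outcomes are measured before and after each session, so a change-score contrast is possible. This stands: the range must carry its conditions. But only wholly uncorrelated pre-post scores bring power near 80%. That is implausible for pain ratings in one person on one day, and the section does not claim it.

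A second reply is that a crossover calculation can land near 34. Bonferroni over nine tests (three primary pain measures by three pairs) at correlation 0 needs 28 completers, or 33 with loss. That is true, but the section states a plain 5% alpha and no such basis. The reply does count against a stronger reading, namely that the authors demonstrably sized a parallel-group trial. The match in step 1 needs the normal approximation with rounding left until after the loss adjustment, and it is not unique. It is an inference about origin.

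A third reply is that the harm is generic. An observed difference below the design value can be significant in any trial with 80% power. With 29 completers and r = 0, p < 0.05 is reached at 2.048 × 2.687 / √29 = 1.02 points. With the 17 completers the paired calculation asks for, it is reached at about 1.38, also below 2. This stands, so the problem is not created by the choice of 34.

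Finally, a condensed article may leave detail to a fuller document. That does not answer the point. The section gives a complete calculation, and its result does not follow for the stated design.

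**Conclusion.** The sample-size statement is wrong as written. For the planned within-person comparison, the stated inputs call for 12 to 20 participants including loss, not 34. With about 29 completers, power for 2 points on one active-versus-placebo contrast is about 97% at correlation 0 and over 99.9% at 0.5 or more. At correlation 0 it is about 92% to 94% with Bonferroni or Tukey over three pairs. The difference detectable at 80% power is about 1.0 to 1.45 points.

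These figures rest on two-sided 5% alpha, non-negative correlation, 15% loss, and 1.9 being a single-session or paired-difference SD. Uncorrelated change scores are the exception, at about 78%.

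A reader might infer that the trial is mis-sized to the point of invalidity, or that its conclusions are compromised. The protocol does not support that. The discrepancy is towards more participants, the trial is not underpowered for 2 points on any plausible reading, and no planned test becomes invalid. This should be fixed, but it does not block the trial.

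**What to change.** Keep 34 participants and rewrite the Sample size paragraph for the crossover. It should state:

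- the contrast powered, for example active versus placebo TENS, and the pain measure it applies to;
- what the SD of 1.9 refers to (single score, change or paired difference);
- an assumed range for the within-person correlation, and the resulting SD of the paired difference, 1.9 × √(2(1 − r)) if 1.9 is a single-session SD;
- the sidedness and the alpha after the planned pairwise adjustment;
- the resulting power for 2 points, or the difference detectable at 80% power, with about 29 completers.

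Add one sentence to the Statistical methods section: the 95% CI of the mean paired difference will be interpreted against the protocol's own 2-point threshold, so that clinical relevance is not read from p < 0.05 alone.

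The cost is one rewritten paragraph and one added sentence. No extra participants, visits or data are needed.
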